### **5. STUDY POPULATION**

#### **5.1. Inclusion Criteria**

In order to be eligible to participate in this study, an individual must meet all of the following criteria:

- Adults (age 18-75 years), men and non-pregnant women
- Overweight or obese (BMI  $\geq 25\text{kg/m}^2$ )
- High waist circumference (USA/Canada  $\geq 102\text{cm}$  in men,  $\geq 88\text{cm}$  in women; Euroid/Caucasian/Middle East, Mediterranean/Sub-Saharan African  $\geq 94\text{cm}$  in men,  $\geq 80\text{cm}$  in women)

women; and Asian [including Japanese]/Ethnic Central and South American  $\geq 90$ cm in men,  $\geq 80$ cm in women[37], with a waist diameter  $\leq 60$  cm)

- Regularly drinking SSBs ( $\geq 1$  servings/day)

We will include participants consuming  $\geq 1$  SSBs servings/day, with 50% enrichment of those consuming  $\geq 3$  SSBs servings/day.

Participants must be agreeable to consume only one study beverage for the duration of the intervention. Participants that are randomized to the 2% soy milk group will be asked to substitute their regular SSB consumption with the 2% soy milk (up to a max of 6 servings/day). Similarly, participants that are randomized to the 2% cow's milk group will be asked to substitute their regular SSB consumption with the 2% cow's milk. All participants must be proficient in English to be eligible for the study. Please see exclusion criteria for a full set of exclusion criteria.

Participants must consent to have the study drinks shipped to their home address by a third-party company, who will not be informed of their participation in the study, or be agreeable to pick up study drinks from the study site at St. Michael's Hospital.

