## 6. STUDY INTERVENTIONS

### 6.1. Interventions

The 3 interventions will consist of  $\geq 1$  servings of (1) 2% soy milk (Alpro Soya[SBI], 250mL single-serve shelf-stable packs, 100Kcal with 8g soy protein per 250mL), (2) 2% cow's milk (Organic Meadows®,

250mL, single-serve shelf-stable packs, 130Kcal with 8g casein/whey protein per 250mL), or (3) usual SSBs (355mL single-serve cans, 130-140kcal per 355mL). The participant's baseline level of intake of SSBs will determine the dose (number of servings). The advantage of this approach is that it represents a 'real-world', 'one-for-one' substitution and allows for a natural dose response. We will cap the maximum allowable number of servings at 6 servings/day, to avoid extreme intakes and ensure that the intake of soy isoflavones does not exceed the generally recognized upper limit of safe intake of 150 mg/day[61, 62]. Although the soy and milk interventions will be matched for protein and serving size, we intentionally did not make the 3 interventions isocaloric, as the goal was to use "real-world" product substitutions. Participants will be instructed to replace their usual SSBs intake with the study beverages while freely consuming their usual background diets. All intervention beverages will be provided. Participants will only receive the beverages that correspond to their group assignment. They will pick up one week of their assigned beverages at each study visit and then will have the remaining three weeks of beverages delivered using an online delivery service (Starhawk/Instacart). Research coordinators will coordinate the beverage disbursements.

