Secondary, exploratory, and adherence outcomes will be assessed by superiority testing among the active treatment (2% soy milk), reference treatment (2% cow's milk), and control treatment (SSB). By reporting all estimated effects and confidence intervals with p-values, the necessary context is provided for a proper interpretation of the statistical evidence [<https://www.tandfonline.com/doi/full/10.1080/00031305.2016.1154108>]. If it is required for a future regulatory submission, then the secondary outcomes will be adjusted for false discovery. The approach will depend on the results of the primary outcome. If the superiority testing of the primary outcome is significant, then we will analyze the secondary outcomes using the Benjamini-Hochberg false discovery rate controlling method with a starting alpha of 0.05 to correct for false discovery [80].

The sample size was selected to allow sufficient power for this analytical approach. The primary analysis will be conducted according to the intention to treat (ITT) principle with IPW to account for any missing values. Data will be analyzed using ANCOVA models for continuous data (mean differences with 95% CIs) and logistic regression models for categorical data (odds ratio with 95% CI for MetS reversion and relative risk with 95% CI for diabetes incidence). Adjustments will be made for age, sex, NAFLD status, medication use, intervention dose (servings/day), and baseline level of the end value. Sensitivity analyses will include completers, per protocol analyses, and ITT with MI.

Prespecified subgroup analyses will be conducted using Chi-square tests by age, sex, NAFLD status, caffeinated beverage use (cola vs non-cola drinkers), intervention dose (servings/day), and baseline waist circumference, FPG, 2hPG, Triglycerides, HDL-C, BP. Continuous linear (dose response gradient) and non-linear (dose response threshold) dose-response analyses will be undertaken over the natural dose response range (3, 4, 5, or 6 servings per day) by multiple linear regression and piecewise regression analyses, respectively.

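### The dose-response analysis is fixed at 3 to 6 servings/day, although participants are enrolled and dosed from 1 serving/day

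*Protocol*

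**What the plan says.** Section 5.1 sets eligibility at 1 or more SSB servings/day, "with 50% enrichment of those consuming" 3 or more. Section 5.2 excludes only intake below 1 serving/day. The synopsis and Section 4.1 repeat the threshold of 1.

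Section 6.1 describes all three interventions as 1 or more servings. The participant's "baseline level of intake of SSBs will determine the dose (number of servings"), which the section presents as a one-for-one substitution that allows a natural dose response. It adds: "We will cap the maximum allowable number of servings at 6 servings/day".

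Section 11 then plans linear (gradient) and non-linear (threshold) analyses over the "natural dose response range (3, 4, 5, or 6 servings per day"), "by multiple linear regression and piecewise regression analyses, respectively".

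The same paragraph says: "Prespecified subgroup analyses will be conducted using Chi-square tests by age, sex, NAFLD status", and goes on to list caffeinated beverage use, intervention dose and several baseline measurements. The paragraph before it sets the models: "Data will be analyzed using ANCOVA models for continuous data (mean differences with 95% CIs"), with logistic regression for categorical outcomes.

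**The concern.** Sections 6.1 and 11 use the same idea, a natural dose response, but give it different ranges. A participant who enters on 1 or 2 servings/day is eligible, randomised and supplied with that number of servings, yet falls outside the range that Section 11 fixes for dose-response.

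Two things are at stake. Precision is lost, because the low end of the range supplies much of the spread in dose. And a piecewise analysis that starts at 3 servings cannot locate a change in slope below 3, where the lighter consumers sit. If the discrepancy stays, someone will also have to choose between 1-6 and 3-6 when the analysis is run, possibly with results in view.

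The subgroup sentence raises a smaller question. It names a Chi-square test without a model, while the primary outcome (liver fat) and all the secondary outcomes are continuous.

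**Working it through.** **Figures in the plan.** The protocol gives no sample size or power for dose-response, so there is none to reproduce. Its main sample size is not at issue, and it reproduces:
- Non-inferiority, with margin 1.5, SD 3, one-sided 0.05 and 80% power: 2 × [3 × (1.645 + 0.842) / 1.5]² ≈ 49.5 per arm; 49.5 / 0.80 ≈ 61.8, hence 62.
- Superiority, with 62 × 0.80 = 49.6 per arm, difference 2, SD 3 and two-sided 0.05: power 0.913, against the stated 91%.

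**Range of dose.**

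| Source | Lower end | Upper end |
|---|---|---|
| 5.1 and 5.2, eligibility | 1 serving/day | – |
| 6.1, dose assigned | 1 serving/day (equals baseline intake) | 6 servings/day (cap) |
| 11, dose-response | 3 servings/day | 6 servings/day |

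The upper ends agree; the lower ends do not.

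**Participants left out.** Number omitted = 186 × (1 − share at 3 or more). The protocol does not give the final share, so it is varied:
- 50%: 186 × 0.50 = 93 (31 per arm). After 20% attrition, 186 × 0.80 × 0.50 ≈ 74 of about 149.
- 60%: 186 × 0.40 ≈ 74 randomised.
- 70%: 186 × 0.30 ≈ 56.
- 80%: 186 × 0.20 ≈ 37.
- Below target, for example 40%: 186 × 0.60 ≈ 112.

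**Precision of a linear slope.** SE = residual SD / √(sum of squares of servings). The ratio of two such SEs does not depend on the SD or on total N, only on the dose distribution. The protocol gives none, so two are assumed, per 100 participants.

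*Even within each half:* 25 each at 1 and 2 servings, 12.5 each at 3, 4, 5 and 6.
- 1 to 6: mean 3.0, variance 3.0, sum of squares 100 × 3.0 = 300.
- 3 to 6: mean 4.5, variance 1.25, sum of squares 50 × 1.25 = 62.5.
- Ratio 62.5 / 300 = 0.21; SE ratio √(300 / 62.5) = 2.19.
- With SD 3 and 148.8 completers: SE 0.14 over 1-6 and 0.31 over 3-6.

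*Skewed to low intake:* 30, 20, 25, 15, 6 and 4 at 1 to 6 servings.
- Variance 1.98 over 1-6 (sum of squares 198) and 0.892 over 3-6 (50 × 0.892 = 44.6).
- SE ratio √(198 / 44.6) = 2.11; SE 0.17 against 0.37.

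These are pooled slopes without covariates. If the arms share one dose distribution, a difference in slopes between arms loses precision by the same factor, because each arm's sum of squares shrinks in the same proportion.

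**The case against.** The case against making much of this is good in several respects.

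- **Reach.** A reader might infer that up to half the trial drops out of the results. The protocol does not support that. The primary superiority, non-inferiority and secondary analyses are not restricted by servings, and servings/day is a covariate in them. Intervention dose is also a prespecified subgroup factor with no lower limit, so participants on 1 or 2 servings do appear in one dose-related analysis.
- **Size.** A reader might take 93 as a maximum. It is not. The 50% enrichment is not defined or stated as a quota, so the number could fall on either side. The 2.2-fold SE likewise rests on an assumed dose distribution.
- **Confounding.** Servings follow habitual intake, so a slope on servings mixes dose with the kind of person who drinks that much. But Section 6.1 says openly how dose is set and claims no randomisation of dose, and multiple linear regression does not rule out arm or arm-by-dose terms. This is a reason to prefer one form of model and does not show an error.
- **Chi-square.** A reader might infer that outcomes will be categorised and the adjustment lost. That follows only if a Pearson test is meant. A Wald or likelihood-ratio test of a treatment-by-subgroup interaction is also a chi-square test and keeps both the continuous outcome and the covariates.

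What the objection does not remove is the range itself. Section 11 states it explicitly, and it disagrees with eligibility and dosing. Because the protocol fixes the range wrongly, this is not a detail left for a statistical analysis plan.

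**Conclusion.** The dose range in Section 11 is wrong as written against the protocol's own Sections 5.1, 5.2 and 6.1. Its effect is confined to the supportive dose-response regressions: participants on 1 or 2 servings/day are omitted, and no threshold below 3 can be detected. The loss is about 93 of 186 if exactly half take 3 or more servings, with about 37 to 74 for shares of 80% to 60%, and more than 93 if enrichment falls short. Under the two assumed dose distributions, the slope SE is about 2.1 to 2.2 times larger than over the full range.

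The sample size and the primary conclusions do not depend on this. The point should be corrected, but it does not threaten the trial. The Chi-square wording is ambiguous and merits only a clarification. No view is taken on which servings rule is right.

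**What to change.** Reconcile Section 11 with Sections 5.1, 5.2 and 6.1 so that the linear and piecewise dose-response analyses cover every dose actually assigned; under the present dosing text that is 1 to 6 servings/day. Preferably fit dose-response as a treatment-by-servings term against the SSB arm in the same ANCOVA. That compares randomised groups at each intake level. It does not make dose itself randomised, and the report should say so.

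As a minor clarification, state that the subgroup Chi-square tests are Wald or likelihood-ratio tests of treatment-by-subgroup interaction within the stated ANCOVA or logistic models, and not Pearson tests on categorised outcomes.

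The cost is two sentences in Section 11, with no new data and no change to any servings rule. The change should be made before unblinded results are seen, so that the range is not chosen with the data in hand.

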## 12. Significance of work

The proposed *Soy Treatment Evaluation on the progression of Metabolic Syndrome (STEM)* trial will strengthen the evidence-base for dietary recommendations that influence public health policy and programs and food procurement policies in public institutions, providing high-quality clinical evidence to support the use of soy as a “public health intervention” for addressing the epidemics of obesity and diabetes and overall metabolic health.

The 3-arm non-inferiority design provides the greatest opportunity for the success of the *STEM* trial. We hypothesize that the active 2% soy milk treatment will be superior to the negative SSBs control treatment. It is also expected to be superior to the reference 2% cow's milk treatment (the ‘standard of care’ from a public health perspective) based on previous head-to-head comparisons of soy milk with cow's milk [7, 31, 32] and soy protein with dairy-derived casein [33]. To protect against the possibility of a lack of superiority, the pre-specification of a non-inferiority comparison with the reference 2% cow's milk requires that it only has to be “as good as” the cow's milk to satisfy the research hypothesis. The present design also still retains the ability to test the superiority of the active 2% soy milk to the reference 2% cow's milk, as we have prespecified rules for testing superiority once non-inferiority criteria has been met. Either finding (non-inferiority or superiority) would represent an actionable outcome for soy, as it would position soy as a healthy alternative to cow's milk for SSBs reduction policies and programs.

## 13. TIMELINE

[figure not shown]

## 14. Genetic Testing

This aspect of the study is not part of the main objectives of the study

### 14.1. Objective

To determine whether there are any genetic differences between individuals in their response to study beverages.

### 14.2. Background

There is considerable interest in the scientific community to study how genes may influence response to diet. In terms of taste our diets tend to be bland containing lower salt and also less sugar. The genes controlling these tastes may therefore determine intake [81, 82]. This is an example of why comprehensive genetic analysis, due to the implication of a growing number of genes of interest, would be helpful. We will, however limit our analyses to specific genes currently known to affect dietary response. Generally, the effect of genes on diet is very modest and usually requires significant numbers of people to detect the difference. It therefore has very limited clinical relevance. We may therefore pool data from across studies, including future studies (typically 30-180 participants per study). We hope to make our initial findings known to participants at the end of the study, especially if we discover specific groups for which certain types of dietary advice may prove advantageous. Genetic testing results are solely for use in this study and will not be shared with any third parties (i.e. insurance companies or the hospital).

### 14.3. Analyses

The DNA will be extracted from “buffy coat” of white blood cells obtained after plasma has been removed from citrated blood samples drawn at week 0 or any time point during the main study. Therefore, no additional blood samples will be required for this study. The genes of interest will include those related to the effectiveness of dietary change on blood glucose, cholesterol and associated measurements including blood pressure, taste preference, and other related genes which may influence response to diet.

